## Abstract

**Background:**

In social neuroscience, the linkage between the endocrinological system and the etiology and symptomatology of mental health problems has received increasing attention. A particular focus is given to the neuropeptide oxytocin with its anxiolytic and stress-buffering effect and the resulting therapeutic potential for anxiety disorders. Even though anxiety disorders are the most prevalent mental health disorders in childhood and adolescence worldwide, the reactivity of the endogenous oxytocin system to an acute stressor (Trier Social Stress Test, TSST) has so far only been investigated in healthy children. It has been shown that peripheral oxytocin levels increased under psychosocial stress conditions. In the present study, it is hypothesized that the endogenous oxytocin system in children and adolescents suffering from a clinically diagnosed anxiety disorder is dysregulated. Three primary outcome parameters will be analyzed: significant differences between participants with anxiety disorders compared to healthy controls in basal oxytocin levels, varying salivary oxytocin release after stress exposure and the correlation between the cortisol peak/-decrease and oxytocin level over time. Secondary outcome criteria are significant differences in physiological (heart rate) and psychological (perceived stress, anxiety, insecurity, tension) responses.

**Methods:**

The present study is a single-center experimental observation study to investigate the reactivity of the endocrinological system to a psychosocial stressor (TSST). 32 children and adolescents (11–18 years) suffering from anxiety disorder will be compared to a matched healthy control group. After a detailed psychological assessment, saliva samples will be taken to measure oxytocin levels before and after psychosocial stress exposure at eight different time points. Additionally, the stress hormone cortisol will be analyzed according to the same procedure.

**Discussion:**

Due to the high prevalence and comorbidity rate with numerous other psychiatric disorders and mental health problems, there is an urgent need to strengthen research in possible neurobiological underpinnings of anxiety disorders. To our knowledge, the proposed experiment is the first study to examine the endocrinological oxytocin and cortisol reaction to an acute psychosocial stressor in children and adolescents with mental health disorders.

*Trial registration* The study is registered in the German Clinical Trials Register since 11 September 2019, DRKS00017793, https://www.drks.de/drks_web/navigate.do?navigationId=trial.HTML&TRIAL_ID=DRKS00017793.

**Supplementary Information:**

The online version contains supplementary material available at 10.1186/s40359-021-00564-z.

## Background

Anxiety disorders are the most prevalent mental health disorders in childhood and adolescence [1, 2]. The Mental Health Module (BELLA study) of the National Health Interview and Examination Survey for Children and Adolescents (KiGGS, Germany) suggests that 1 out of 10 children and adolescents aged 7–17 shows mental health problems associated with high levels of anxiety [3]. Anxiety disorders can lead to mental health problems along with adverse physiological functioning and impairments in adulthood [4, 5] and have high comorbidity rates with numerous other psychiatric disorders such as depressive disorders (comorbidity rate ranges from 50 to 72%) [5]. Whereas anxiety disorders such as phobias, social anxiety and separation anxiety have a very early age of onset between 5 and 10 years, others (generalized anxiety disorder, panic disorder) tend to have a later age of onset between 24 and 50 years [6]. Due to the high number of younger patients, it is an essential task for early prevention to investigate the etiopathology of anxiety disorders, particularly in childhood and adolescence.

Of particular interest is the relevance of endocrinological functions to the onset and course of mental diseases. With a better understanding of the endocrinological system and its effects on social behavior, it may be possible to develop new drug therapy strategies in addition to psychotherapeutic approaches. According to the guidelines of the German Society for Child and Adolescent Psychiatry, Psychosomatics and Psychotherapy (DGKJP), classical psychotropic drugs such as tricyclic antidepressants and benzodiazepines do not show adequate effects in children on panic disorders, and neither do tricyclics on separation anxiety disorders [7]. Tricyclics are less preferred in the treatment of anxiety in children due to their potential for cardiac abnormalities [8] and benzodiazepines because of their marked side effects such as the development of addiction [9]. Merely the efficacy of Selective Serotonin Reuptake Inhibitors (SSRIs) on generalized anxiety disorders and separation anxiety disorders in childhood and adolescence has been confirmed with limitations (for review see [10–12]).

In clinical neuroscience, worldwide the neuropeptide oxytocin (OXT) has started to receive increasing attention for its role in mental health and stress regulation [13–16]. Several recent studies with healthy humans and adult patients with social anxiety disorder describe a reduction of experienced anxiety and a stress-buffering effect of intranasal (i.n.) OXT (e.g. [14, 17]).

OXT is primarily synthesized in magnocellular neurons in the paraventricular and supraoptic nuclei of the hypothalamus and released into the systemic circulation by the posterior pituitary [17]. OXT acts as a neurohormone as well as a neuromodulator in many OXT-Receptors (OXTR) expressing brain regions such as the hypothalamic nuclei and extrahypothalamic limbic areas [18]. In addition to the central OXT and OXTR expression, OXTR and OXT synthesis have also been detected in peripheral organs [14, 19]. The OXT concentration can be quantified in the cerebrospinal fluid as well as in blood plasma, urine and saliva samples representing either the cerebral or peripheral OXT system [20]. Since fearful and stressful conditions activate the endogenous OXT system and consequently, central as well as peripheral OXT is being released, peripheral saliva OXT can be assessed as a global marker of the OXT system and to some extent represents the central activity of the individual OXT system to stress [15].

Numerous studies in animals and healthy adult volunteers have demonstrated an anxiolytic and prosocial effect of OXT (for review see [15, 16]). OXT seems to play an important role in human social cognition, motivation, emotion detection, emotion recognition [21] and emotional memory as well as prosociality such as trusting behavior, generosity and cooperation [22–26]. OXT modulates the salience processing of external social cues constrained by personality characteristics and different contextual factors [23, 25]. Human neuroimaging studies have demonstrated altered amygdala reactivity reflecting different i.n. induced OXT activity in nodes of the salience network [25]. Compared to placebo for example, after i.n. OXT administration, participants with post-traumatic stress disorder (PTSD) and borderline personality disorder showed decreased amygdala activity towards angry vs. happy faces. In contrast, healthy participants showed increased activity [25]. The individual and population-specific effects of exogenous i.n. OXT and modulational effects on social salience depending on individual factors might reflect the differences in the endogenous OXT response between various populations [23]. Neumann and Slattery [15] hypothesized that higher cerebral OXT activity is associated with less expression of fear. Patients who exhibited a current diagnosis of PTSD and participants with a history of childhood maltreatment had much higher peripheral blood OXT levels than healthy controls [13]. It was assumed that an acute release of peripheral and central OXT in stressful situations provides a natural mechanism for the reduction of stress and anxiety [27]. Lebowitz et al. [28] described that children with separation anxiety had a significant (*p* < 0.01) decrease in basal saliva OXT levels (16.7 pg/ml, SD = 706) compared to anxious children not meeting criteria for separation anxiety (26.8 pg/ml, SD = 15.6). The authors concluded that children with separation anxiety have greater reliance on the support of primary attachment figures which leads to an additional decrease in OXT level. It is assumed that attachment representations affect stress responses and positively predict OXT levels [29, 30]. Pierrehumbert et al. [30] noted that participants with insecure attachment showed elevated levels of subjective stress and moderate levels of OXT during the TSST. Participants with secure attachment reported relatively low subjective stress and presented high levels of OXT. Due to the correlation between OXT, attachment and stress response [29–31] as well as the evidence of other animal and human studies [15], it is hypothesized that the etiology of anxiety disorders, particularly those with a social component, may be associated with an imbalance of the endogenous OXT system.

Despite the high prevalence of anxiety disorders in adolescents (11–18 years), the potential therapeutic use and anxiolytic effect of OXT (see above), as well as the influence of stress on the endogenous OXT system of children and adolescents, have only been investigated in one study with healthy volunteers by Bernhard et al. [32]. In a standardized laboratory setting the authors demonstrated that the peripheral OXT level increased under psychosocial stress conditions (using the TSST [33]). In addition, this study concluded that low basal OXT levels were associated with greater expression of anxiety and insecurity during stressful situations. Children and adolescents with a primary low basal OXT level showed a greater increase in OXT during the TSST. In contrast, a higher basal OXT level correlated subsequently with less anxiety [32]. Even though childhood experiences influence the regulation of OXT release in adulthood [13], there is no comparable trial investigating the response of the endogenous OXT system to an acute stressor in children and adolescents with psychiatric disorders, in particular, anxiety disorders compared to a control group of same-aged healthy participants without psychiatric diagnoses.

In the study by Bernhard et al. [32], the salivary cortisol (CORT) concentration was examined as a second neurophysiological parameter of stress reaction. The adrenal cortical hormone CORT is an elementary component of the hypothalamic–pituitary–adrenal (HPA) axis and the endocrinological stress regulation system. A meta-analysis by Cardoso et al. [34] supported the hypothesis that OXT plays an important role in the etiology of HPA dysfunction associated with psychopathology. The detailed interplay of OXT and CORT under stress conditions has rarely been studied [32]. In a human study in 2003, Heinrichs et al. [35] were the first to observe that the combination of i.n. OXT and social support suppressed CORT levels under stress conditions (TSST) and resulted in increased calmness and decreased anxiety. In healthy participants i.n. OXT, as well as natural high baseline OXT concentrations in saliva, appear to be correlated with low CORT response and less anxiety in stressful situations [32, 35, 36]. In contrast, lower baseline OXT was associated with higher CORT levels and greater OXT reactivity [32]. To the best of our knowledge, the only study addressing this relationship in children and adolescents was conducted by Bernhard et al. [32]. In the study, healthy children and adolescents showed an earlier peak of salivary OXT at + 1 min after stress compared to the CORT level at + 10 min after stress. Furthermore, they showed an earlier decrease of OXT to the baseline level compared to CORT after stress exposure was terminated [32]. Based on the earlier OXT peak, the authors assumed that OXT has a regulatory effect on CORT, which may act as a support mechanism during stressful situations [32]. In the present study, we expect a dysregulated interplay between OXT and CORT under stress [34] in children and adolescents suffering from anxiety disorder compared to healthy controls. If children and adolescents with anxiety disorder show a low basal OXT level (see above), there are two possible assumptions on the interplay between OXT and CORT. On the one hand, since low basal OXT levels in healthy participants correlated with a higher increase of saliva OXT and CORT during the TSST [32], we expect participants with anxiety disorder to show less increase of OXT, thereby reflecting a pathological lacking stress-buffering mechanism [15] and a subsequently higher expression of subjective stress and anxiety [35, 37]. On the other hand, because of the HPA axis co-activation and greater stress-induced OXT reactivity associated with faster vagal recovery, Engert et al. [38] rather suggested a “recovery-boosting” than a “reactivity-buffering” effect. With respect to previous research, however, the influence of OXT on the HPA axis under stress has not been fully determined yet, especially regarding clinical populations. Recent findings describe a blunted CORT response to psychosocial stress (TSST) in women with anxiety disorder [39] and patients with panic disorder [40, 41]. These findings led to the hypothesis of a HPA-axis hypo-responsiveness in patients with mental health disorders, promoting high vulnerability during acute stress response. This was also found in studies with adolescents with non-suicidal self-injury (NSSI) [42].

Due to the controversial findings [32, 35, 38], there is an urgent need for further research to improve our knowledge on the interplay of OXT and CORT under stress in psychiatric compared to healthy participants [35].

### Objectives

With the purpose of a better understanding of the linkage between dysregulation of the endogenous OXT system and the etiology of anxiety disorders, the present study aims to investigate three questions as main outcome objectives. First, it will be investigated whether basal saliva OXT levels of children and adolescents (11–18 years of age) with a clinically diagnosed anxiety disorder (experimental group) differ significantly from OXT levels of healthy children and adolescents without a clinical psychiatric diagnosis (healthy control group). The second question addresses whether children and adolescents of the experimental group show a significant change in the salivary OXT level to an acute stressor (TSST) compared to healthy controls. Regarding the key role of CORT in stress regulation, the third question addresses the differences of both groups between the in- and decrease of salivary CORT in relation to the OXT level under stress conditions. Secondary outcome criteria are significant differences in physiological (heart rate) and psychological (perceived stress, anxiety, insecurity, and tension) responses between both groups.

As an additional exploratory question, the severity of anxiety symptoms and the partial influence of comorbid psychiatric conditions such as depression will be evaluated.

### Primary hypothesis

It is hypothesized, that the endogenous OXT system of children and adolescents (11–18 years of age) suffering from a clinically diagnosed anxiety disorder is dysregulated. As different types of anxiety disorders in children have been associated with dysregulation of the HPA-axis [43], no differences between different types of anxiety disorders in response to stress are expected. A lower basal OXT level of the experimental group, as well as less OXT release as a response to an acute stressor, is expected, compared to the control group. In both groups, it is assumed that the OXT level peaks and decreases earlier than the CORT level. We expect a negative correlation between basal OXT level and CORT increase in both groups. Basal OXT and OXT increase under stress are expected to correlate positively with subjective stress level (VAS). OXT increase is expected to correlate positively with vagal recovery. In healthy controls, we anticipate a positive correlation between OXT release and CORT release. As described in the background section, in participants with anxiety disorders two controversial hypotheses about the interplay between CORT and OXT under stress will be discussed. First, participants with anxiety disorders might show low OXT increase correlating with high CORT increase reflecting a pathological, lacking stress-buffering effect of OXT. Second, participants with anxiety disorders might show low OXT increase correlating with attenuated CORT response reflecting HPA-axis hypo-responsiveness.

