It is expected that participants suffering from anxiety disorders show a lower basal OXT level than healthy controls. If this is indeed the case, future studies may be able to achieve a therapeutic effect by raising basal OXT levels in clinical cohorts. As moderate anxiety and a lower basal OXT level correlated with higher OXT release during the TSST in healthy children and adolescents [32], the expected reduced OXT release of participants with anxiety disorders and a high level of anxiety may suggest the presence of a pathological lacking compensation mechanism. Since it has been shown that the OXT level peaks and decreases earlier than the CORT level [32], a present correlation between OXT level and CORT level suggest that OXT may influences the CORT release and subsequently the subjective stress response. Therefore, if less OXT is released, we expect a higher increase of CORT and respectively a higher subjective stress response. Alternatively, attenuated CORT release might support recent findings with the hypothesis of a CORT hypo-responsiveness in patients with anxiety disorder [39, 40, 42]. Identifying whether there is indeed such a relationship between OXT and CORT is crucial for the in-depth understanding of the stress response in children and adolescents suffering from anxiety disorders.

Potential limitations and challenges of the present study include the fact that the hormonal system is influenced by many external factors, such as pubertal status, sex and parent–child attachment. Therefore, a detailed inspection of the eligibility criteria (see Data Assessment) and a corresponding matching of the control group is highly important. All participants will be carefully examined with detailed questionnaires and categorical diagnoses will be assessed using a semistructured diagnostic interview in addition to routine clinical diagnostics.

For the healthy controls, the study provides the benefit of being screened by psychiatric professionals. If an unpredictable psychiatric abnormality is detected, the affected participant can be admitted directly to the in- or outpatient clinic of child and adolescent psychiatry, psychosomatics and psychotherapy at the University of Regensburg and hence receive help.

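### The third primary outcome asks whether the oxytocin–cortisol relation differs between groups, but the listed analyses do not compare it, and the second patient hypothesis predicts the same sign as in healthy controls

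*Protocol article*

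**What the plan says.** All references are to the protocol article.

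- **Abstract.** One of the three primary outcome parameters is "the correlation between the cortisol peak/-decrease and oxytocin level over time".
- **Objectives.** This is put as a contrast between groups: "the third question addresses the differences of both groups between the in- and decrease of salivary CORT in relation to the OXT level" under stress.
- **Background.** The expectation for patients relative to controls is stated: "In the present study, we expect a dysregulated interplay between OXT and CORT under stress".
- **Primary hypothesis, controls.** "In healthy controls, we anticipate a positive correlation between OXT release and CORT release".
- **Primary hypothesis, patients.** Two rival hypotheses are given: "First, participants with anxiety disorders might show low OXT increase correlating with high CORT increase reflecting a pathological, lacking stress-buffering effect of OXT", and "Second, participants with anxiety disorders might show low OXT increase correlating with attenuated CORT response reflecting HPA-axis hypo-responsiveness".
- **Statistical analysis, relation between the hormones.** FDR-corrected correlations are planned among OXT and CORT baseline, increase and recovery; whether by group or pooled is not said. If correlations are significant, CORT increase is regressed on OXT increase, CORT baseline and group. A further regression of CORT recovery uses OXT increase and CORT increase.
- **Statistical analysis, mean levels.** An rmMANOVA with time and group, and MANOVAs of baseline, increase and recovery, compare the groups' OXT and CORT values.

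**The concern.** The objective is a difference between groups in an association. The analyses that address the association estimate it without contrasting the groups, and the analyses that contrast the groups do so for means. The hypotheses straddle the two: they are worded as correlations, yet the second describes a level.

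Two misreadings become possible. If the relation really is reversed in patients, no listed analysis shows that it differs from controls. If the relation is the same in both groups, a positive patient correlation can be presented as hypo-responsiveness although it is what the protocol predicts for health. The text does not say which result would count against a dysregulated interplay.

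**Working it through.** The plan gives no figure for this point. Power calculation uses f = 0.4 and f = 0.25 and states no OXT–CORT correlation. The group size of 32 and alpha of 0.05 are the plan's; two-sided testing and every r and mean shift below are assumptions.

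**1. Predicted signs (Primary hypothesis)**

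| Group | Prediction | Implied sign |
|---|---|---|
| Controls | OXT and CORT release rise together | + |
| Patients, first hypothesis | low OXT with high CORT | − |
| Patients, second hypothesis | low OXT with attenuated CORT | + (as controls) |

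Only the first differs from controls in sign.

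**2. A within-group correlation ignores level**

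For constants a and b, corr(X + a, Y + b) = corr(X, Y). Lowering every patient's CORT increase by the same amount leaves r unchanged. Simulation with 4000 trials per scenario, 32 + 32 bivariate-normal participants, control r = 0.4 and patient mean shifts of 0.8 SD:

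| Scenario in patients | Mean patient r | Mean pooled r | CORT mean comparison rejects | Correlation-difference test rejects |
|---|---|---|---|---|
| Same r, same means | 0.39 | 0.40 | 4.9% | 5.0% |
| Same r, low OXT, low CORT | 0.39 | 0.48 | 88.7% | 5.4% |
| Same r, low OXT, high CORT | 0.39 | 0.20 | 87.8% | 4.6% |
| r = −0.4, low OXT, high CORT | −0.39 | −0.14 | 88.2% | 90.5% |
| r = 0, low OXT, low CORT | 0.00 | 0.31 | 87.2% | 37.2% |

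The first three rows have the same patient correlation, whether CORT is normal, blunted or raised. Only the comparison of mean CORT increase detects the blunted response.

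**3. What the listed analyses would show if the first hypothesis were true**

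- *Pooled correlation.* With equal groups, unit within-group variances and mean differences d(OXT) and d(CORT), pooled r = [mean within-group covariance + d(OXT) × d(CORT)/4] / √{[1 + d(OXT)²/4] × [1 + d(CORT)²/4]}. With r = +0.4 and −0.4, d(OXT) = −0.8 and d(CORT) = +0.8, this is (0 − 0.16)/1.16 = −0.14, as simulated. The critical |r| at N = 64 is 1.999/√(62 + 1.999²) = 0.246. If the correlations are pooled, a true reversal of sign would often fail to trigger the conditional regression.
- *Regression.* Ignoring CORT baseline, a model with OXT increase and group but no product term fits one common slope. With equal group sizes and variances that slope is (0.4 − 0.4)/2 = 0. The reversal averages out.
- *rmMANOVA and MANOVAs.* These compare mean profiles and mean summary scores, not the association.

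**4. What a direct comparison could achieve at 32 per group**

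Fisher z: SE = √(2/(32 − 3)) = 0.263; power ≈ Φ(|atanh r₁ − atanh r₂|/SE − 1.96).

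- +0.4 v −0.4: 0.847/0.263 = 3.23; Φ(1.27) ≈ 0.90.
- +0.3 v −0.3: 0.619/0.263 = 2.36; Φ(0.40) ≈ 0.65.
- Equal correlations, as the second hypothesis allows: 0.05.

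**The case against.** **Hypo-responsiveness is testable as the plan stands.** The MANOVAs compare the groups on CORT increase, and the Discussion links hypo-responsiveness to attenuated CORT release, which is a level. This stands, and it makes the fix cheap. What is missing is the link: Primary hypothesis words the idea as a correlation and does not point to that comparison.

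**The wording may mean group profiles, low/high against low/low.** That is a fair reading. On it, however, the hypotheses concern means, and a correlation outcome does not test them. Either reading calls for rewording.

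**The hypotheses are openly competing and are only to be discussed.** Leaving the direction open where earlier findings conflict is legitimate. They nevertheless stand under Primary hypothesis and bear on a primary outcome.

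**A condensed article may leave such detail to a fuller plan.** That would excuse silence. Here the regression predictors are spelled out, and as listed they do not match the stated objective.

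Three stronger readings are tempting but not supported:

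- *That no correlation could count against the hypotheses.* A near-zero patient correlation fits neither one.
- *That the planned regression fails.* Its stated purpose is to quantify the variance in CORT increase explained by OXT increase independently of CORT baseline. It is not presented as a test of group or of hypo-responsiveness.
- *That the Discussion treats any correlation as causal.* The sentence containing "a present correlation between OXT level and CORT level suggest that OXT may influences the CORT release and subsequently the subjective stress response" is hedged and leans on OXT peaking earlier than CORT, not on the correlation alone.

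**Conclusion.** The point holds in a limited form. For the third primary outcome, the objective (a group difference in the OXT–CORT relation), the hypotheses and the listed analyses do not line up. The first patient hypothesis is not tested as a group difference. The second shares its sign with the prediction for health, and a within-group correlation cannot show it.

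That a correlation does not respond to a mean shift is a mathematical fact and needs no assumed value. The sizes (about 5% against about 89% rejection under the second hypothesis; about 65% to 90% power for a direct comparison under the first) rest on assumed correlations and 0.8 SD shifts that the documents do not supply.

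The problem is confined to this outcome. The expectations of lower basal OXT and of less OXT release in patients are directional and can be refuted. It should be corrected before analysis but does not undermine the design.

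**What to change.** 1. **Statistical analysis.** Add an OXT-increase-by-group term to the CORT-increase regression, or compare the two groups' correlations directly. Run it whether or not the correlations are significant. Tie the lacking-buffer hypothesis to it: a negative relation in patients that differs from controls.
2. **Primary hypothesis.** Tie hypo-responsiveness to the group comparison of CORT increase already planned, without OXT increase in that model. State that a positive correlation in patients alone is not evidence for it.
3. **Primary hypothesis.** State that similar OXT–CORT relations in both groups, with no difference in mean CORT increase, count against a dysregulated interplay.

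The cost is wording and one extra contrast; no new data are needed. The drawback is limited power at 32 per group: about 90% for an assumed +0.4 v −0.4, about 65% for +0.3 v −0.3, and about 37% if the patient relation is merely absent (+0.4 v 0). A non-significant contrast should therefore be reported with its confidence interval and not taken by itself as proof that the relations are alike.
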